### Inclusion/exclusion criteria

2.3

Inclusion criteria for the subjects of this study are detailed below:

Adults (females or males) older than 18 years old with a diagnosis of T2D in the clinic database.Patients who have been taking the combination therapy of metformin + sodium-glucose transport protein 2 inhibitors (iSGLT2), as recommended by the redGDPS 2023, with stable medication for the past 6 months.Diabetic patients taking prescribed VitD treatment for at least 6 months (intervention group) and diabetic patients not taking prescribed VitD (control group).Patients who signed the informed consent.Patients capable of performing mild to moderate physical activity (to walk steadily and independently for at least 6 min).

Exclusion criteria of subjects are summarized below:

Patients taking other medication different than metformin + iSGLT2 (including combinations and insulin).Patients with severe or uncontrolled chronic diseases (e.g., cardiovascular, hepatic, renal, or musculoskeletal disorders) that could interfere with exercise performance, metabolic outcomes, or overall safety.Patients taking polyvitaminic supplementation at the inclusion for at least, 1 month before the intervention.Female subjects who are pregnant.Patients who did not sign the informed consent.

### Endpoints

2.4

#### Primary endpoint

2.4.1

The primary endpoint of the DIAVITEX trial is the change in insulin resistance, measured by the HOMA-IR index, from baseline to week 16.

#### Secondary endpoints

2.4.2

Secondary endpoints include:

Changes in glycemic parameters (HbA1c, fasting glucose, fasting insulin).Changes in lipid profile (total cholesterol, HDL, LDL, triglycerides).Changes in inflammatory markers (C-reactive protein, interleukin-6, TNF-*α*).Changes in anthropometric parameters (weight, BMI, waist circumference, skinfold thickness).Changes in psychological well-being and adherence to the Mediterranean diet.Safety outcomes, including incidence of hypo-and hyperglycemia and any adverse events related to the intervention.

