#### Food consumption and adherence to the Mediterranean diet

2.5.2

Nutritional questionnaires will be provided in person during the first visit at the participating pharmacies, right after recruitment. Adherence to the Mediterranean dietary pattern will be determined using the Mediterranean Diet Adherence Screener (MEDAS) developed in the PREDIMED study. MEDAS is a questionnaire consisting of 14 questions. Values of 0 or 1 are assigned to each item, the maximum adherence to the Mediterranean Diet is indicated by a 14-point score (26). A validated food frequency questionnaire (FFQ) with 137 items plus specific questions for patterns of alcohol consumption and vitamin/minerals supplements will also be administered (adapted from the Willett questionnaire and validated in Spain) (27).

The inclusion of these dietary assessments aims to provide valuable insights into the eating habits of the selected population before the study. Based on the participant’s diet, during the study we will reinforce the recommendations of the Spanish Society for Diabetes. Nutritional education programs based on the previously mentioned recommendations will be provided to participants, where adaptations can be designed to participant particular needs (age, gender, activity, DM treatment, etc.) (28). Moreover, the gathered data will also serve to normalize the overall diet of all participants during the study.

In addition to the questionnaires, dietary intake and adherence will be briefly reviewed during the follow-up via monthly telephone interviews and pharmacy visits to check consistency of responses and reinforce adherence. Participants may also keep short dietary notes or logs if feasible.

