#### Blood sampling and analysis

2.5.4

A total of 2 blood samples will be obtained during the study. The analyses will be conducted at the following times:

After the first visit, at baseline, and before the intervention (complete blood analysis, including VitD).At the end of study, at month 4, after the exercise intervention (complete blood analysis, including VitD).

All subjects will go in the morning at their respective Primary Care Centers after 12 h of fasting. Blood sampling will be performed at the corresponding CAP. Blood samples will be analyzed by the Servei de Bioquímica Clínica (Hospital Universitari Vall d’Hebron).

The blood parameters to be determined are the following:

Vit D (cholecalciferol)InsulinGlucoseGlycosylated hemoglobinTotal CholesterolLDL cholesterolHDL cholesterolTriglyceridesHepatic profileMicroalbuminuriaHemogramRenal functionC reactive proteinErythrocyte sedimentation rateFerritin

HOMA-IR index will also be calculated as previously described (31) by using formula (HOMA-IR = fasting glucose in mmol/l*fasting insulin in μU/ml/22.5) to determine insulin resistance. HOMA-B index to quantify the pancreatic beta cell function using formula (HOMA-B360 x fasting insulin (μU/mL)/(fasting glucose (mg/dL)−63)) will be determined.

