**Figure 1 fig1:**
[figure not shown]
Design of patient 6 visits throughout the study.

An initial visit at the pharmacy will be performed (in person) with the participants (visit 2). During this visit, the investigator pharmacist from Blanquerna will obtain the signed informed consent, collect basic sociodemographic data (age, weight, height, and gender), and will perform the nutritional and well-being questionnaires and duration of current medication. Further, information about the personal trainer, the training schedule and the corporate Teams meeting links and password will be provided. During the first meeting, the participant will be provided with: the recommendations for a healthy diet by the Spanish Society of Diabetes and a nutritional proposal based on the abovementioned guidelines (33).

Two additional monthly check-ups, consisting of a short telephone interview (covering any adverse events, general well-being, etc.) will be performed 2 and 3 months after study initiation (visit 3 and visit 4).

A final visit at month 4 (visit 5), will be performed at the end of the study, in the pharmacy office where the well-being questionnaire and a satisfaction questionnaire will be provided. Upon completion of the study at the pharmacies, a second blood test at CAP Sant Rafael will be requested by the CAP physician; this procedure will take place during the 6th visit.

Pharmacists will oversee the follow-up, to ensure safety through rigorous monitoring and reporting procedures. Any concerning findings will be promptly addressed, and appropriate measures will be taken to safeguard participant health and ensure the integrity of the study results.

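### IL-6 and TNF-alpha are secondary endpoints but are not on the list of blood parameters to be measured; the month-4 time point for MEDAS and anthropometry should also be stated

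*Protocol article*

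**What the plan says.** **Inflammatory markers.** Section 2.4.2 defines a secondary endpoint as "Changes in inflammatory markers (C-reactive protein, interleukin-6", with TNF-alpha completing the bracket. Section 2.5.4 states that "A total of 2 blood samples will be obtained during the study", one at baseline and one at month 4, and introduces its panel with "The blood parameters to be determined are the following". The panel that follows has CRP, erythrocyte sedimentation rate and ferritin, but no IL-6 and no TNF-alpha.

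**Diet and anthropometry.** Section 2.4.2 also names "Changes in anthropometric parameters (weight, BMI, waist circumference, skinfold thickness" and "Changes in psychological well-being and adherence to the Mediterranean diet". On timing, section 2.5.2 says "Nutritional questionnaires will be provided in person during the first visit at the participating pharmacies, right after recruitment", and that including these assessments "aims to provide valuable insights into the eating habits of the selected population before the study". Section 2.9 records weight and height at visit 2. It describes the final pharmacy visit (visit 5, month 4) as taking place "in the pharmacy office where the well-being questionnaire and a satisfaction questionnaire will be provided"; visit 6 is the second blood test. Section 2.5.1 describes BMI and skinfolds without time points, does not name waist, and ends by placing anthropometry under the ISAK standard.

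**Analysis.** Section 2.11 applies ANCOVA adjusted for baseline to the inflammatory, anthropometric, dietary and well-being outcomes.

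**The concern.** A change endpoint analysed by baseline-adjusted ANCOVA needs a value at both ends. For IL-6 and TNF-alpha the article provides neither: one section promises the endpoints, and the section that tells the laboratory what to measure omits them. The panel is specific enough to name ferritin and microalbuminuria, and nothing in its wording suggests that it is only a selection.

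For MEDAS and anthropometry the question is narrower. The endpoints are plainly meant to be measured twice, but the text does not say where the second measurement takes place.

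The stake is the same in both cases. A month-4 measurement that is not taken cannot be obtained later. A cytokine not ordered at baseline is also lost, unless serum has been kept, on which the article is silent.

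**Working it through.** The article gives no figure to reproduce. The check takes each continuous measure in 2.4.2 and looks for a baseline and a month-4 value in sections 2.5.1 to 2.5.4 and 2.9.

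| Measures in 2.4.2 | Number | Baseline in text | Month 4 in text |
|---|---|---|---|
| HbA1c, fasting glucose, fasting insulin | 3 | yes (2.5.4) | yes (2.5.4) |
| Total cholesterol, HDL, LDL, triglycerides | 4 | yes (2.5.4) | yes (2.5.4) |
| CRP | 1 | yes (2.5.4) | yes (2.5.4) |
| Psychological well-being | 1 | yes (2.5.3, 2.9) | yes (2.5.3, 2.9) |
| IL-6, TNF-alpha | 2 | not on the panel | not on the panel |
| Weight, BMI | 2 | yes (2.9, visit 2) | not stated |
| Mediterranean-diet adherence (MEDAS) | 1 | yes (2.5.2, 2.9) | not stated |
| Waist, skinfolds | 2 | time not stated | time not stated |

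Total: 3 + 4 + 1 + 1 + 2 + 2 + 1 + 2 = 16 measures. Both values are provided for in 3 + 4 + 1 + 1 = 9. The other 2 + 2 + 1 + 2 = 7 are of two kinds.

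1. **IL-6 and TNF-alpha (2 of 7): a contradiction.** Counting the 2.5.4 panel gives vitamin D, insulin, glucose, HbA1c, total cholesterol, LDL, HDL, triglycerides, hepatic profile, microalbuminuria, hemogram, renal function, CRP, erythrocyte sedimentation rate and ferritin: 15 items, neither cytokine among them. So 2 of the 3 named inflammatory markers have no assay at either draw.

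2. **Weight, BMI, waist, skinfolds and MEDAS (5 of 7): unstated timing.** The evidence is strongest for MEDAS. Section 2.5.2 sets it at the first pharmacy visit and gives its purpose as describing diet beforehand. Section 2.5.3, by contrast, says outright that well-being is assessed before and after, and visit 5 includes the well-being questionnaire. For anthropometry there is only silence: weight and height appear at visit 2, nothing appears at visit 5, and waist and skinfolds have no time point at either end.

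HOMA-IR uses fasting glucose and insulin. Both are on the panel at both draws, so the primary endpoint can be computed.

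**The case against.** A reader might infer that the diet and anthropometric endpoints cannot be computed at all, and that none of the 80 participants would have a follow-up value. The documents do not support that, for four reasons.

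- **The visit narrative in 2.9 is not a complete list of assessments.** For visit 2 it omits the skinfolds described in 2.5.1 and the activity questionnaire that 2.5.3 places at that same visit. It does not mention the before-and-after fitness tests in the Abstract or the monthly pharmacy visits in 2.7. If omission meant not done, skinfolds would be missing at baseline too. Silence at visit 5 is therefore weak evidence.
- **Figure 1, the diagram of the six visits, is not shown.** It may list more assessments. A full protocol may also carry a schedule that a journal article condenses.
- **Other text points towards repeat measurement.** The endpoints are defined as changes, 2.11 analyses them with baseline adjustment, 2.5.2 has diet reviewed briefly at later contacts, and 2.5.5 includes dietary questionnaires in the pharmacist's follow-up role. None of this states a month-4 MEDAS, but together it shows the intent.
- **Waist is covered in general terms** by the ISAK sentence in 2.5.1, although no specific procedure is given.

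These arguments stand, and they reduce the second part to a request for clarity. They do not touch the cytokines. A visit diagram would not by itself remove the conflict between the endpoint list and the laboratory panel, and nothing else in the article resolves it. That all seven measures are secondary endpoints in a trial described as exploratory limits the consequence, but does not remove the conflict.

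**Conclusion.** The cytokine point holds with high confidence. Sections 2.4.2 and 2.5.4 contradict each other, and if the panel is followed, 2 of 3 inflammatory endpoints have no data at either time point. This assumes only that the panel means what its introduction says.

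The MEDAS and anthropometry point holds with lower confidence, and only as unstated timing for five measures. It has direct textual support for MEDAS and rests largely on silence for weight, BMI, waist and skinfolds. Sight of Figure 1 or of a full assessment schedule could settle it.

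The damage is confined to secondary endpoints; the primary analysis is untouched. The reason to act is that the repair is small and uncollected data cannot be recovered.

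**What to change.** **Reconcile 2.4.2 with 2.5.4, by one of two routes.**

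- Add IL-6 and TNF-alpha to the 2.5.4 panel for the two existing draws, before the first participant is sampled. The cost is two assays: for 80 participants, 2 markers × 2 draws × 80 = 320 determinations. The article gives no price. This keeps the declared endpoints and fits the Introduction, which cites both markers in the rationale.
- Or remove both from 2.4.2 by a documented amendment and keep CRP. This saves the assays but changes the declared outcomes, so the amendment should be dated and give its reason.

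**State the month-4 time point.** In 2.5.1, 2.5.2 and 2.9, say that MEDAS, weight, waist and skinfolds are taken at baseline and repeated at visit 5, and name waist among the 2.5.1 measurements. BMI then follows from weight and the recorded height. The cost is a few minutes at a visit that already takes place. If Figure 1 or the full protocol already schedules these, aligning the text is enough.

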### Study design

2.1

The DIAVITEX study is a randomized controlled clinical trial involving medicinal products, designed in accordance with Real Decreto 957/2020 of November 3rd, which regulates observational studies with human-use medicinal products. The trial framework is superiority, designed to test whether the combination of aerobic and resistance training with ongoing VitD treatment is superior to either intervention alone or control in improving insulin resistance.

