### Safety

2.10

Measures to ensure the safety of participants include a thorough medical screening prior to enrollment, and a close monitoring of patients’ health status during intervention. Safety protocols also include the role of participating healthcare centers in case of any medical concerns or emergencies during the trial.

All adverse events, including hypoglycemia, hyperglycemia, musculoskeletal injuries, fatigue, and any other exercise-related symptoms, will be systematically collected. Adverse events will be assessed at each training session, at each pharmacy follow-up visit, during monthly telephone interviews, and at the final visit. The type, severity, and potential relation to the intervention will be documented. Serious adverse events will be reported immediately to the study’s principal investigators and the Ethics Committee. No interim efficacy analysis is planned due to the exploratory nature of this trial; however, the study will be stopped if ≥20% of participants in any arm experience serious adverse events related to the intervention.

In addition, participants will be provided with information on participating community pharmacies to receive appropriate assistance if needed. Additionally, participants will be educated on signs and symptoms of hypo-and hyperglycemia and instructed on appropriate actions to take if these occur during or after exercise sessions. The trial protocol also includes provisions for modifying or discontinuing exercise interventions based on individual participant responses and safety concerns identified during the trial.

Physical activity is not expected to produce adverse events. Nonetheless, physical activity programs will be individualized based on the needs and characteristics of each participant. If any adverse events related to physical activity are detected, patients can go to healthcare centers following standard practice.

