### Statistical analysis

2.11

All data will be reported as mean and standard deviation. Data normality and homogeneity of variance will be tested using Shapiro–Wilk and Levens tests, respectively. The primary endpoint (change in HOMA-IR) from baseline to 16 weeks, will be analyzed using ANCOVA with group as the fixed factor, baseline HOMA-IR as covariate, and VitD treatment status included as a stratification variable. Secondary continuous outcomes (glycemic, lipid, inflammatory, anthropometric, dietary, and psychological well-being measures) will also be analyzed with ANCOVA, adjusting for baseline values. Categorical outcomes (e.g., adverse events) will be compared using χ^2^ or Fisher’s exact test. Bonferroni *post hoc* test will be used if there is a significant difference between the groups. Exploratory analyses will test for interaction effects between exercise and VitD status using factorial ANOVA models; these analyses are considered hypothesis-generating due to sample size limitations. In addition, exploratory analyses will be performed to examine potential sex-related differences in primary and secondary outcomes. Sex will also be included as a covariate in the statistical models when appropriate. Statistical power will be calculated by *post hoc* power analysis method by using G Power software.

The results will be analyzed using SPSS (version 22) for Windows. The significant level (*α*) of all statistical analyses will be 0.05.

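### The adverse-event endpoint in 2.4.2 counts related events, while 2.10 and 2.11 collect and compare all adverse events; a between-group test on related events would be biased against exercise

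*Protocol article*

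**What the plan says.** Three sections of the protocol article describe the adverse-event outcome.

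- **2.4.2 Secondary endpoints** gives "Safety outcomes, including incidence of hypo-and hyperglycemia and any adverse events related to the intervention". The relatedness qualifier is attached to the adverse events; hypo- and hyperglycaemia incidence is a separate item.
- **2.10 Safety** states that "All adverse events, including hypoglycemia, hyperglycemia, musculoskeletal injuries, fatigue, and any other exercise-related symptoms, will be systematically collected", and adds that "The type, severity, and potential relation to the intervention will be documented". Relatedness is a recorded attribute here, not a filter.
- **2.11 Statistical analysis** states that "Categorical outcomes (e.g., adverse events) will be compared using χ^2^ or Fisher’s exact test". It does not mention relatedness.

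The term intervention is not used in one sense. Only exercise is randomised (2.2), and 2.7 calls the training programme the primary intervention model. But 2.1 speaks of a combination that "is superior to either intervention alone or control in improving insulin resistance", 2.3 labels the VitD users as the intervention group, and the stopping rule in 2.10 applies relatedness to any arm. The hypothesis in the Introduction describes the control group as having no intervention. Section 3.1 concedes that the possibility to blind is restricted.

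**The concern.** The section that fixes the endpoint and the sections that collect and compare the data name different variables. An analyst who follows 2.4.2 tests related events; one who follows 2.10 and 2.11 tests all events. The two are not equally suited to a between-group test.

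A participant assigned to no exercise cannot have an event caused by the exercise programme. A test of related events across arms therefore sets the exercise groups against a count that is fixed at zero in advance. It measures how often staff attribute an event to exercise, not whether exercise changes the event rate. Fatigue or muscle pain that is equally common in all arms would count against exercise only, and adverse events that exercise prevents would not show at all. Because blinding is restricted, the attribution would in general be made by people who know the allocation.

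**Working it through.** The plan states no adverse-event rate or power for this comparison, so there is no figure to reproduce. The check has two parts.

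**1. Who can score on the related-event component** (20 per group, Table 1)

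| Group | Intervention = exercise | Intervention = exercise or VitD |
|---|---|---|
| 1 Exercise + VitD | can score | can score |
| 2 Exercise, no VitD | can score | can score |
| 3 VitD, no exercise | cannot | can score |
| 4 Neither | cannot | cannot |

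So 40 of 80 participants cannot score on the first reading, and 20 of 80 on the second.

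**2. What a test against a fixed zero can show**

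Inputs: 40 exercise and 40 no-exercise participants (2 × 20 each). Section 2.11 says the significance level "of all statistical analyses will be 0.05"; it does not give sidedness, so two-sided is taken. It also does not say which groups are contrasted; exercise against no exercise is used because exercise is the randomised factor. The intervention is taken to mean exercise.

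For x/40 against 0/40 with equal groups, the two-sided Fisher p-value is 2 × C(40, x) / C(80, x):

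- x = 5: 2 × 658,008 / 24,040,016 = 0.0547
- x = 6: 2 × 3,838,380 / 300,500,200 = 0.0255

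Significance therefore needs at least 6 related events in the exercise half.

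Let the true risk of an adverse event be equal in all arms, and let a share of exercise-arm events be labelled related. The labelled rate is q = risk × share, and the chance of a false exercise-worse result is P(X ≥ 6) with X ~ Bin(40, q). Risks and shares are assumptions.

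| True risk, all arms | Share labelled related | q | Chance of false result (Fisher) |
|---|---|---|---|
| 20% | 25% | 0.050 | 1.4% |
| 30% | 25% | 0.075 | 7.6% |
| 40% | 25% | 0.100 | 20.6% |
| 20% | 50% | 0.100 | 20.6% |
| 30% | 50% | 0.150 | 56.8% |
| 40% | 50% | 0.200 | 83.9% |

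Outside this range the chance can be negligible: at 20% risk with a tenth labelled related (q = 0.02) it is about 0.01%.

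For comparison, Fisher's test on all-cause counts in both halves with equal risks of 20% to 40% is significant in either direction about 3% of the time, so about 1.4% in the exercise-worse direction. That assumes events are found equally often in all arms.

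On the wider reading of intervention, only Group 4 is a structural zero. Group 2 against Group 4 then needs 5/20 against 0/20 (p = 0.047; 4/20 gives 0.106). The chance of a false result is 0.3% at q = 0.05 and 37% at q = 0.20.

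Uncorrected chi-square would be significant from 4/40 against 0/40 (p = 0.040). The expected event count there is only 4/2 = 2 per half, where Fisher's test would normally be chosen, so the chi-square figures are not relied on.

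**The case against.** The strongest reply is that 2.10 and 2.11, read together, already give a sound plan: all events are collected, relatedness is an attribute, and the test is named for adverse events without a qualifier. On that reading 2.4.2 is loose wording, and the choice of counts to test could be left to an analysis plan that is not shown. It stands that 2.11 does not commit the trial to the biased test. It does not settle the matter, because 2.4.2 is where the endpoint is defined and its wording selects the variable that is poorer for a comparison between arms. That is a conflict in the text, not a missing detail.

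Stronger readings are tempting, and the documents do not support them:

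- **That the whole safety endpoint counts only related events.** Hypo- and hyperglycaemia are listed separately, on the natural reading without the qualifier, and the list is open-ended. They can be scored in all four groups.
- **That both no-exercise groups are zero by construction.** This holds for Group 4. For Group 3 it requires the intervention to mean exercise, and 2.1, 2.3 and the stopping rule in 2.10 use the word more widely.
- **That the planned test will show harm.** It can. Significance depends on event rates and attribution shares that the documents do not give, and 2.10 says only that physical activity is not expected to produce adverse events.

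**Conclusion.** The inconsistency between 2.4.2 and sections 2.10 and 2.11 is real and should be resolved before analysis. If related events are the variable tested, the estimate is biased against exercise as soon as any event is labelled related, and a significant difference can arise with equal true rates. On a 40 against 40 comparison by Fisher's test this takes at least 6 related events. Its chance is about 1% to 84% for assumed true risks of 20% to 40% with a quarter to a half labelled related. These figures rest on the intervention meaning exercise and on the assumed rates and shares; the direction of the bias does not depend on the particular rates. The point concerns one component of one secondary endpoint in a trial that calls itself exploratory. It does not touch the primary endpoint or the hypo- and hyperglycaemia outcomes.

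**What to change.** In 2.4.2, define the adverse-event endpoint as the proportion of participants with at least one adverse event of any cause, in all four groups, and keep hypo- and hyperglycaemia incidence as its own item. In 2.11, state that the chi-square or Fisher comparison applies to these all-cause counts. Report related events descriptively in the exercise arms, with no between-group test. State what the intervention means in the relatedness assessment.

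The cost is wording only, because 2.10 already provides for collecting all events with their relation to the intervention; no new data or visits are needed. There is a small downside: background events enter the count and dilute a true exercise-specific harm, which the descriptive listing keeps visible.

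One limit remains. Section 2.10 says that "Adverse events will be assessed at each training session, at each pharmacy follow-up visit, during monthly telephone interviews, and at the final visit". The no-exercise arms have no training sessions, so their events have fewer occasions to be found, and all-cause counts are not fully free of ascertainment bias. The report should say so.
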